### **Rationale for Non-Inferiority Margin**

The non-inferiority margin ( $\Delta = 0.8\%$ ) was selected based on clinical and statistical justifications. Although the anticipated difference between the ICE and TEE groups is only 0.1%, the margin reflects the maximum clinically acceptable increase in thromboembolic risk, as supported by prior literature and expert consensus. In the context of extremely low event rates (0.5% – 0.6%), using a wider margin allows for a feasible study sample size without compromising patient safety or trial integrity. Furthermore, demonstrating that the upper limit of the 95% confidence interval remains within the 0.8% margin ensures clinical comparability. This design strategy is consistent with FDA and EMA guidance for non-inferiority trials with binary safety endpoints.

## **3.3 Eligibility Criteria**

258 Participants undergoing atrial fibrillation ablation on a stable, uninterrupted regimen  
259 of oral anticoagulation for at least 3 weeks—either with a vitamin K antagonist (with  
260 INR maintained between 2.0 and 3.0) or with a direct oral anticoagulant (DOAC)—  
261 were eligible for enrollment.

## 262 **Inclusion Criteria**

263 Participants must meet all of the following criteria:

- 264 1. Aged 18 to 80 years
- 265 2. Diagnosed with paroxysmal, persistent, or long-standing persistent AF based  
266 on ECG or Holter
- 267 3. Scheduled to undergo radiofrequency catheter ablation
- 268 4. Able and willing to provide written informed consent

## 269 **Exclusion Criteria**

270 Participants will be excluded if they meet any of the following:

- 271 1. End-stage disease with a life expectancy of less than 1 year.
- 272 2. Severe heart failure, defined as New York Heart Association (NYHA)  
273 functional class III or IV, or a most recently documented left ventricular  
274 ejection fraction (LVEF) <30%.
- 275 3. History of prior AF treatment with surgical or catheter ablation.
- 276 4. Bradyarrhythmia requiring pacemaker therapy or the presence of an  
277 implanted implantable cardioverter-defibrillator (ICD).
- 278 5. Recent major cardiovascular events, including acute myocardial infarction  
279 (AMI), any percutaneous coronary intervention (PCI), cardiac valve surgery,  
280 or percutaneous valvular intervention within the past 3 months.
- 281 6. Stroke or transient ischemic attack (TIA) within the past 6 months.
- 282 7. Active systemic infection or sepsis at the time of enrollment.
- 283 8. Contraindications to TEE, including but not limited to esophageal disease  
284 (e.g., esophageal stricture, esophageal varices), recent upper gastrointestinal  
285 bleeding, or severe coagulopathy.
- 286 9. Participation in another investigational study involving devices or  
287 pharmaceutical agents within the past 30 days.
- 288 10. Women of childbearing potential who are pregnant, breastfeeding, or  
289 planning to become pregnant during the study period.

290

## 291 **3.4 Interventions**

### 292 **ICE Group (Intervention Arm)**

ICE imaging was performed using a 10F SoundStar probe (Biosense Webster Inc., Diamond Bar, CA), which was inserted through an 11F hemostatic sheath positioned in the left femoral vein. ICE catheters are equipped with a linear-phased array multi-frequency (5.5-10 MHz) transducer and connected to the Vivid I system (GE Healthcare, Waukesha, WI).

## Procedure Steps:

### 1. Positioning the ICE Catheter:

- The tip of the ICE catheter was placed inside the mid-right atrium and rotated clockwise until the LAA was visualized.
- Subsequently, the ICE probe was positioned parallel to the His bundle to obtain long-axis imaging of the LAA.
- The probe was then advanced into the right ventricular outflow tract (RVOT) and pulmonary artery (PA) to achieve better visualization of the LAA.

[figure not shown]

Figure 2. Detection of thrombus of LA/LAA from different positions

### 2. Minimized Fluoroscopy Strategy:

- During procedures utilizing the ICE catheter, a strategy of minimized fluoroscopy was employed, although achieving zero radiation exposure was not mandatory.
- Specifically, ICE catheter and CARTSOUND™ integrated real-time ICE imaging were utilized for:
  - Geometry construction
  - Transseptal puncture
  - Effusion monitoring

319                   ○ Minimal fluoroscopy was utilized at each step as determined feasible  
320                   by the individual operator.

321 This approach ensures comprehensive imaging while minimizing patient exposure to  
322 radiation. The use of real-time ICE imaging facilitates precise procedural guidance  
323 and enhances safety during complex cardiac interventions.

324

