## 2.2 Objectives

The primary objective of this study is to evaluate whether ICE is non-inferior to TEE in excluding LA or LAA thrombus prior to AF ablation. By accurately identifying patients without thrombus, the study aims to determine whether ICE can serve as a safe and effective alternative imaging modality, potentially reducing thrombus-related procedural complications and improving procedural workflow.

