## 2.3 Trial Design

This study is a multicenter, prospective, randomized, open-label, parallel-group, non-inferiority trial. A total of 1810 patients undergoing AF ablation were randomized 1:1 to receive either ICE-guided or TEE-guided thrombus screening. Outcome assessors, including the Clinical Endpoint Committee (CEC), are blinded to group allocation.

[figure not shown]

Figure 1. Trial design

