### 325 **TEE Group (Control Arm)**

- 326           • Thrombus screening performed within 24 hours pre-procedure using standard  
327           TEE (GE Vivid E9 or Philips iE33).
- 328           • Multiplanar views including mid-esophageal four-chamber view, mid-  
329           esophageal two-chamber view, mid-esophageal long-axis view, transgastric  
330           short-axis view, deep transgastric long-axis view and upper esophageal aortic  
331           arch view.
- 332           • Transseptal puncture guided by fluoroscopy.

333

334 TEE images were first evaluated by an experienced echocardiographer and  
335 subsequently reviewed by at least two other experienced echocardiographers who  
336 were blinded to the results of the initial TEE. This meticulous procedure ensures  
337 comprehensive cardiac assessment and quality control through multiple expert  
338 reviews.

339

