## Secondary Endpoints

The prespecified secondary endpoints include:

- The detection rate of thrombus.
- Death related to the radiofrequency ablation procedure.
- Major bleeding complications: pericardial effusions and cardiac tamponade.
- Minor bleeding complications: vascular complications such as pseudoaneurysms, arterio-venous fistulas, and hematomas.
- Procedural characteristics: total procedure time, fluoroscopy time, and radiofrequency delivery time.
- Pre-procedural psychological state: Assessed using the Hospital Anxiety and Depression Scale (HADS), 14a self-assessment questionnaire measuring anxiety and depression levels in patients receiving medical care. Higher scores indicate more severe symptoms.
- Procedural pain degree: Measured using the Numeric Rating Scale (NRS), where patients rate their pain on a scale from 0 (no pain) to 10 (worst possible pain).
- Hospitalization cost: Expenses incurred during a patient's hospital stay, including charges for medical services, procedures, medications, accommodations, and other related expenses.
- Preprocedural waiting time: The period of time a patient waits before undergoing ablation.

These well-defined endpoints will help the researchers assess the effectiveness, safety, and patient experience of using ICE compared to TEE in patients undergoing AF ablation.

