## 4. Methods: Assignment of Interventions

### 4.1 Allocation

This study employs a **simple computerized randomization** strategy with a 1:1 allocation ratio. Eligible participants are randomly assigned to undergo thrombus screening with either ICE (ICE group) or TEE (TEE group) before catheter ablation.

The randomization schedule is generated using validated, centralized computer software to ensure adequate allocation concealment. Allocation occurs **after patient enrollment and informed consent**, and prior to the start of imaging and ablation procedures.

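### The protocol says it randomises thrombus screening, but the arms also differ in procedural guidance, so the trial compares two whole strategies rather than two screening tests

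*Protocol*

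**What the plan says.** Three places define the comparison as one of screening methods.

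- Section 2.2: the primary objective is to "evaluate whether ICE is non-inferior to TEE in excluding LA or LAA thrombus prior to AF ablation".
- Section 2.3: patients are "randomized 1:1 to receive either ICE-guided or TEE-guided thrombus screening".
- Section 4.1: "Eligible participants are randomly assigned to undergo thrombus screening with either ICE (ICE group) or TEE (TEE group) before catheter ablation".

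Section 3.4 describes what each arm receives.

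- **ICE arm**, under the minimised-fluoroscopy heading: "During procedures utilizing the ICE catheter, a strategy of minimized fluoroscopy was employed". The text continues that "ICE catheter and CARTSOUND™ integrated real-time ICE imaging were utilized for" three tasks: building the geometry, transseptal puncture and watching for effusion. It credits real-time ICE with a benefit of its own: it helps guide the procedure "and enhances safety during complex cardiac interventions".
- **TEE arm**: "Transseptal puncture guided by fluoroscopy". Nothing is said about limiting fluoroscopy or about how effusions are monitored.
- **Both arms**: ablation catheter, CARTO3, mapping catheter, lesion settings and ACT range. None of the ICE-arm additions appears here.

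Section 3.5 makes periprocedural stroke, TIA and systemic embolism the primary endpoint. Its secondary endpoints include pericardial effusion and tamponade, and "Procedural characteristics: total procedure time, fluoroscopy time, and radiofrequency delivery time".

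**The concern.** Two factors change together between the arms: the screening test and the guidance used during the ablation. The protocol treats them as separable. Section 2.1 describes ICE for puncture guidance and complication monitoring as routine, and its use for detecting appendage thrombus as emerging.

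The primary endpoint counts embolic events during and after the procedure, so it can respond to either factor. In a non-inferiority trial a benefit from guidance could offset harm from missed thrombi, and a harm from guidance could hide adequate screening. In neither case would the result answer the objective in section 2.2.

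For fluoroscopy time no assumed effect is needed. One arm follows a strategy of minimising fluoroscopy and the other has fluoroscopic puncture, so a difference cannot be credited to screening.

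**Working it through.** **Step 1. Set the arms side by side (section 3.4).**

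| Element | ICE arm | TEE arm | Stated for both arms? |
|---|---|---|---|
| Screening | ICE | TEE | no, the stated factor |
| Transseptal puncture | real-time ICE | fluoroscopy | no, explicit contrast |
| Geometry | ICE in addition to mapping catheter | mapping catheter | mapping catheter only |
| Effusion monitoring | real-time ICE | not stated | no |
| Fluoroscopy | minimised, as far as the operator finds feasible | no instruction stated | no |
| Ablation settings, ACT range | same | same | yes |

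Only the puncture contrast is explicit for both arms. The effusion and fluoroscopy contrasts are inferred from their appearing only under the ICE arm.

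**Step 2. Sort the endpoints by when they arise.**

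- Before puncture and ablation, so not affected by these co-interventions: thrombus detection, preprocedural waiting time, pre-procedural HADS.
- During or after them, so open to both factors: embolic events (primary), fluoroscopy time, procedure time, effusion/tamponade.

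**Step 3. What the randomised contrast identifies.** Write the risk difference as

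RD = S + G,

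where S is the effect of screening and G the effect of guidance, including any interaction. The trial estimates RD. With one contrast and two unknowns, S is identified only if G = 0, and no section states or supports that.

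**Step 4. How much G could matter (illustration only).** The protocol gives no value for G, so its size here is assumed. Inputs: margin 0.8%, TEE rate 0.5% and ICE rate 0.6% (section 3.2); 1810/2 = 905 per arm (section 2.3); Farrington–Manning limits (section 5.4, Statistical Methods).

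The plan's own figure first: 7.84 × 0.010939 / 0.000049 = 1750.24, against 1750.45 printed. It reproduces in substance and has no bearing on this point.

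Non-inferiority is declared when (p̂₁ − p̂₂ − 0.008)/SE < −1.96, with SE from the restricted estimates. The probabilities are exact sums over binomial outcomes.

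(a) Screening truly worse by exactly the margin (0.5% + 0.8% = 1.3% against 0.5%), with guidance lowering ICE-arm risk by an assumed relative amount:

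| Assumed reduction | ICE rate | RD | Chance of declaring non-inferiority |
|---|---|---|---|
| 0% | 1.30% | 0.80 | 1.9% |
| 10% | 1.17% | 0.67 | 3.7% |
| 20% | 1.04% | 0.54 | 6.8% |
| 30% | 0.91% | 0.41 | 12.1% |
| 40% | 0.78% | 0.28 | 20.6% |
| 50% | 0.65% | 0.15 | 33.2% |

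(b) Screening as planned (0.6% against 0.5%), with guidance raising ICE-arm risk by an assumed 0%, 10%, 25% or 50% (to 0.60%, 0.66%, 0.75% or 0.90%): the chance is 39.2%, 32.0%, 23.1% or 12.6%.

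The 39.2% lies below the planned 80% because section 3.2 uses a per-arm result as a total. That is a separate matter. The two panels show only that G can push the conclusion either way.

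**The case against.** The best reply is that this is a strategy trial and is open about it. The title speaks of periprocedural complications of ICE and TEE and mentions neither screening nor thrombus. Section 2.1 justifies the primary endpoint by reference to strategies, and section 3.5 closes by speaking of using ICE compared with TEE in ablation patients. Section 3.4 discloses the whole bundle. Using an ICE catheter that is already in place for puncture and monitoring is a reasonable pragmatic choice, and randomisation compares the two strategies validly. All of this stands. It does not remove the mismatch, because the objective, the design statement and the allocation section still name screening.

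The reply also rules out several stronger readings that a reader might infer.

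- *None of the results can be attributed to screening.* Too broad: the three endpoints that precede puncture are not affected.
- *The primary result is biased towards ICE, or the margin is in effect wider by a known amount.* The safety remark in section 3.4 is generic and does not concern embolism, and no section gives an effect of guidance on embolic events. The ICE catheter also needs an 11F femoral sheath and is advanced into the outflow tract and pulmonary artery, so the net direction is open.
- *Effusions were sought continuously by ultrasound in one arm and not at all in the other.* The protocol does not say continuously, and it is silent on monitoring in the TEE arm.
- *Fluoroscopy time is fixed in advance.* The strategy depends on operator feasibility, and zero radiation was not mandatory.

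**Conclusion.** The point holds as a mismatch between the stated question and the delivered interventions. As written, the trial can support a conclusion about an ICE-based strategy against a TEE-based strategy. It cannot support one about the screening tests alone from the embolic endpoint, fluoroscopy time, procedure time or effusion/tamponade.

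The puncture contrast is explicit. The contrasts in effusion monitoring and fluoroscopy rest on the assumption that what is listed only under the ICE arm was not part of TEE-arm care.

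No numerical size can be put on the effect on the primary endpoint. The illustration rests on assumed effects, and zero effect is compatible with the documents.

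**What to change.** 1. In sections 2.2, 2.3 and 4.1, state the comparison as an ICE-based strategy (ICE screening plus ICE-guided procedure) versus a TEE-based strategy (TEE screening plus fluoroscopy-guided puncture), and limit the non-inferiority conclusion to that. If a comparison of screening alone is intended, section 3.4 must be reconciled with those three sections. How procedures are performed in either arm is for the investigators.
2. Report fluoroscopy time as descriptive, or as a feature of the strategy, and not as evidence for ICE screening.
3. Interpret procedure time and effusion/tamponade as strategy outcomes, noting that real-time ICE effusion monitoring is specified only for the ICE arm.

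The cost is wording and a narrower claim, with no extra patients, procedures or data.

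Two further analyses may suggest themselves but add little. Separating effusions by how they were detected needs data that section 5.1 does not list. Splitting the primary result by puncture method largely reproduces the arm comparison, with about 905 × 0.006 = 5.4 and 905 × 0.005 = 4.5 expected events per arm.

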### 325 **TEE Group (Control Arm)**

- 326           • Thrombus screening performed within 24 hours pre-procedure using standard  
327           TEE (GE Vivid E9 or Philips iE33).
- 328           • Multiplanar views including mid-esophageal four-chamber view, mid-  
329           esophageal two-chamber view, mid-esophageal long-axis view, transgastric  
330           short-axis view, deep transgastric long-axis view and upper esophageal aortic  
331           arch view.
- 332           • Transseptal puncture guided by fluoroscopy.

333

334 TEE images were first evaluated by an experienced echocardiographer and  
335 subsequently reviewed by at least two other experienced echocardiographers who  
336 were blinded to the results of the initial TEE. This meticulous procedure ensures  
337 comprehensive cardiac assessment and quality control through multiple expert  
338 reviews.

339

### 340 **Ablation Procedure (Both Groups)**

- 341           • Ablation performed using THERMOCOOL SMARTTOUCH® SurroundFlow  
342           catheter under CARTO3 guidance.
- 343           • PentaRay® mapping catheter used for 3D reconstruction.
- 344           • Ablation strategy: pulmonary vein isolation (PVI) as standard, with lesion  
345           settings: 35–50W power, AI targets: 450–550 (anterior), 350–450 (posterior),  
346           – Saline flow as per manufacturer guidelines.
- 347           • Intraprocedural activated clotting time (ACT) was monitored at regular  
348           intervals, with intravenous heparin administered to maintain an ACT between  
349           300 and 350 seconds throughout the procedure.

350

## 351 **3.5 Endpoints**

## Primary Endpoints

The primary endpoint centers on thromboembolic events occurring during the periprocedural period, which encompass:

- Stroke: Characterized as an abrupt onset of neurological dysfunction resulting from disrupted cerebral blood flow, causing tissue damage. Diagnosis is confirmed via MRI or CT imaging.
- Transient Ischemic Attack (TIA): A brief episode of neurological dysfunction due to temporary interruption of blood supply to a localized area of the brain. Symptoms typically resolve within 24 hours.
- Systemic Embolism: Sudden blockage of a blood vessel by an embolus, resulting in tissue ischemia or infarction in an organ other than the brain.

## Secondary Endpoints

The prespecified secondary endpoints include:

- The detection rate of thrombus.
- Death related to the radiofrequency ablation procedure.
- Major bleeding complications: pericardial effusions and cardiac tamponade.
- Minor bleeding complications: vascular complications such as pseudoaneurysms, arterio-venous fistulas, and hematomas.
- Procedural characteristics: total procedure time, fluoroscopy time, and radiofrequency delivery time.
- Pre-procedural psychological state: Assessed using the Hospital Anxiety and Depression Scale (HADS), 14a self-assessment questionnaire measuring anxiety and depression levels in patients receiving medical care. Higher scores indicate more severe symptoms.
- Procedural pain degree: Measured using the Numeric Rating Scale (NRS), where patients rate their pain on a scale from 0 (no pain) to 10 (worst possible pain).
- Hospitalization cost: Expenses incurred during a patient's hospital stay, including charges for medical services, procedures, medications, accommodations, and other related expenses.
- Preprocedural waiting time: The period of time a patient waits before undergoing ablation.

These well-defined endpoints will help the researchers assess the effectiveness, safety, and patient experience of using ICE compared to TEE in patients undergoing AF ablation.

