## 2. Introduction

### 2.1 Background and Rationale

Atrial fibrillation (AF) is the most common sustained cardiac arrhythmia, characterized by rapid and irregular atrial electrical activity. This disrupts effective atrial contraction and hemodynamics, leading to blood stasis in the left atrial appendage (LAA) and significantly increasing the risk of thrombus formation. Studies have shown that the incidence of LAA thrombi in anticoagulated patients with AF ranges from 0.4% to 15.2%, depending on individual characteristics and comorbidities. The presence of LAA thrombus is considered an absolute contraindication to catheter ablation. Once detected, the procedure must be postponed until adequate anticoagulation therapy has resolved the thrombus.

Transesophageal echocardiography (TEE) has long been regarded as the gold standard for preprocedural LAA thrombus screening, with a reported sensitivity and specificity exceeding 90%. TEE enables high-resolution imaging by positioning an ultrasound probe in the esophagus, close to the heart. In a global survey of AF ablation centers, 73.2% reported routine use of TEE before ablation, regardless of patients' CHA2DS2-VASc scores. However, despite its diagnostic accuracy, TEE is semi-invasive and associated with discomfort and procedural risks such as gag reflex, sedation-related complications, and even esophageal injury. Additionally, when image quality is suboptimal, the sensitivity of TEE to exclude LAA thrombi is reduced. The proportion of equivocal TEE findings has been reported to be as high as 17.8%, leading to potential misdiagnosis and procedural delays.

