#### 440 **Outcome and Follow-Up Data**

- 441       • Thromboembolic events (stroke, TIA, systemic embolism)
- 442       • Complications: bleeding, tamponade, vascular injury
- 443       • Pain and anxiety scores (NRS and HADS)
- 444       • Hospitalization cost and duration
- 445       • Follow-up visits at 1 week, 2 weeks, and 1 month post-procedure

- Adverse events and serious adverse events (SAEs)

All collected data are entered in real time or within 14 days of each study visit, and validated by the site principal investigator.

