### **5.4 Statistical Methods**

#### **Primary Analysis Population**

- Modified intention-to-treat (mITT): all randomized patients who underwent ablation
- Per-protocol (PP): patients who completed imaging and ablation per assigned group without major protocol violations

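### The secondary safety endpoints include none of the TEE harms that the rationale names, and the death endpoint as worded leaves out a death caused by screening before ablation

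*Protocol*

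**What the plan says.** Section 3.5 of the protocol (Secondary Endpoints) lists three clinical safety items:

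- The death item reads "Death related to the radiofrequency ablation procedure".
- Major bleeding is confined to effusion into the pericardium and tamponade.
- The vascular item reads "Minor bleeding complications: vascular complications such as pseudoaneurysms, arterio-venous fistulas, and hematomas".

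Section 2.1 gives the reasons for seeking an alternative to TEE, among them that "TEE is semi-invasive and associated with discomfort and procedural risks such as gag reflex, sedation-related complications, and even esophageal injury". The same section ends by including safety among the things to be compared between ICE and TEE, and the closing sentence of Section 3.5 says the endpoints serve to assess safety.

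On timing and access, Section 3.4 describes TEE as "Thrombus screening performed within 24 hours pre-procedure using standard" equipment, so it is a separate examination before the ablation. The ICE probe is introduced in the ablation setting, "which was inserted through an 11F hemostatic sheath positioned in the left femoral vein".

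On data capture, Section 5.1 names "Complications: bleeding, tamponade, vascular injury" as the complication items. It separately lists adverse events and serious adverse events, with visits at 1 week, 2 weeks and 1 month after the procedure. Section 5.4 defines the modified intention-to-treat set as "all randomized patients who underwent ablation".

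**The concern.** The randomised contrast is the screening test, so the harms of the tests themselves are part of the safety question. The endpoint list was drawn up around the ablation: bleeding into the pericardium, injury at the access site, and death attributed to the ablation. Harm from the extra ICE sheath can register under the vascular item. Harm from passing a TEE probe, or from any sedation given for it, has no item to register under.

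The death endpoint adds a second difficulty. It counts a death only if it is related to the ablation. A death caused by TEE hours before the ablation does not meet that wording.

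What is at stake is the secondary safety comparison. One of the stated motives for replacing TEE would go untested by any prespecified endpoint.

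**Working it through.** The plan gives no figure on this point, so there is none to reproduce. The check sets the harms against the endpoints that could count them.

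| Harm | Where the protocol raises it | Clinical safety endpoint in Section 3.5 that counts it |
|---|---|---|
| Oesophageal injury | Section 2.1 | None |
| Sedation-related event | Section 2.1 | None |
| Gag reflex, discomfort | Section 2.1 | None; pain (NRS) and HADS may reflect part of it, but neither is tied to the TEE examination |
| Injury at the ICE venous access | Section 3.4 (11F sheath) | Vascular complications |
| Pericardial effusion, tamponade | Section 3.5 | Major bleeding, both arms |
| Death attributed to ablation | Section 3.5 | Death endpoint, both arms |
| Death caused by the screening test before ablation | Not raised | None, unless it is a thromboembolic death counted in the primary endpoint |

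The named complication items in Section 5.1 show the same pattern: bleeding, tamponade and vascular injury, with nothing oesophageal or sedation-related. Such an event would enter the database only as a general AE or SAE.

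**Scale.** Inputs:

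- TEE patients: 1810 / 2 = 905 (target in Section 1.2 and Section 2.3, 1:1 allocation).
- TEE-specific harm rate: not in the protocol. Assumed range 0.1% to 1.0%.
- Primary event rates: 0.5% (TEE) and 0.6% (ICE), from Section 3.2.

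Expected uncounted events = 905 × rate; chance of at least one = 1 − (1 − rate)^905.

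| Assumed rate | Expected events in 905 | Chance of at least one |
|---|---|---|
| 0.1% | 0.9 | 60% |
| 0.2% | 1.8 | 84% |
| 0.5% | 4.5 | 99% |
| 1.0% | 9.05 | over 99.9% |

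For comparison, the expected primary events per arm are 905 × 0.005 = 4.5 and 905 × 0.006 = 5.4.

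**Direction.** The uncounted harms belong to the control test. Leaving them out lowers the apparent harm in the TEE arm, which works against ICE on safety. The primary endpoint (stroke, TIA, systemic embolism) contains none of these harms, so its analysis does not change.

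**The case against.** The strongest reply is that nothing is lost. AEs and SAEs are recorded in both arms (Section 5.1), monitors check that they are documented (Section 6.2), and the DSMB and the Steering Committee review safety data or SAEs (Sections 1.5 and 6.1). The AE tables to be produced can be left to an analysis plan that is not shown. This stands as far as data capture goes, and a reader who infers that the trial can say nothing about TEE harm goes too far. It does not supply a prespecified endpoint, and the endpoint list is fixed in the protocol.

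Four other stronger readings are tempting, and the protocol does not support them.

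- *Only one arm's harms are counted.* Pericardial and vascular events are counted in both arms, and both arms undergo the same ablation. Transseptal puncture is guided differently in the two arms, so these endpoints could favour either. Only the extra sheath is specific to ICE.
- *A patient who dies before ablation drops out of every analysis.* The modified intention-to-treat set is defined under the primary analysis population. Nothing says that deaths or AEs are confined to it. The protocol also does not say that they are counted in all randomised patients, so this needs stating.
- *Relatedness of deaths is judged unblinded.* Section 1.5 gives a blinded, independent CEC all relevant safety endpoints, and Section 6.1 includes major complications. Section 4.2 names only thromboembolic and bleeding events when it describes the blinding. Whether death is covered is unclear; it is not shown to be unblinded.
- *The missing events rival the primary events in number.* That follows only from the upper part of an assumed range. Exclusion criterion 8 removes patients with contraindications to TEE, which should lower the rate, and Section 3.4 does not say whether TEE is done under sedation.

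It can also be argued that Section 2.2 ties safety to thrombus-related complications, and that Section 8.2 shows a deliberate narrowing of the endpoints. Both are fair readings of those sections, but Section 2.1 and the closing sentence of Section 3.5 claim a wider safety comparison.

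**Conclusion.** The point holds as a gap in the secondary endpoints. The listed safety endpoints omit the TEE harms that the protocol itself gives as reasons to look for an alternative, and the death endpoint as worded does not reach a death caused by screening before ablation. They therefore cannot give a balanced safety comparison of the two tests.

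The gap tends to understate harm in the TEE arm. A reader might suspect that it helps ICE to a false non-inferiority result. It does not: it works against ICE on safety, and the primary endpoint and margin are unaffected.

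The size cannot be derived from the protocol. The figure of about 1 to 9 events in 905 rests wholly on the assumed 0.1% to 1.0%. Deaths will be few, so counting all deaths removes a judgement about cause and adds little power.

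**What to change.** Make two changes to Section 3.5, both analysed in all randomised patients by assigned arm:

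1. Report death from any cause to the 1-month visit, and keep procedure-related death as a subset. The visit is timed from the procedure, so state the time origin for patients who never reach ablation.
2. Add a secondary endpoint of screening-test complications: oesophageal or pharyngeal injury, aspiration, sedation or airway events, and ICE-catheter events not already counted as vascular or pericardial. Count from the start of imaging. The last restriction keeps sheath events from being counted twice.

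Both can be drawn from the AE and SAE data already collected. The costs are some AE coding and a few more cases for the CEC. The new endpoint will have few events and will mix events of different severity, so its components should be listed separately. Some ICE-catheter events will still need a judgement on whether the screening or the ablation caused them, and that should go to the blinded committee. Ascertainment may be incomplete unless the eCRF prompts for these items, because Section 5.1 now names only bleeding, tamponade and vascular injury. The sample size and the primary analysis stay as they are.
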